# Laser therapy for onychomycosis in patients with diabetes at risk for foot complications: study protocol for a randomized, double-blind, controlled trial (LASER-1)

**DOI:** 10.1186/s13063-015-0622-4

**Published:** 2015-03-22

**Keywords:** Onychomycosis, Nd:YAG laser, Diabetic foot, Diabetic foot ulcer

## Abstract

**Background:**

In a sham-controlled double-blind trial, we aim to establish the efficacy and safety of the local application of laser therapy in patients with diabetes, onychomycosis and risk factors for diabetes-related foot complications. Onychomycosis leads to thickened and distorted nails, which in turn lead to increased local pressure. The combination of onychomycosis and neuropathy or peripheral arterial disease (PAD) increases the risk of developing diabetes-related foot complications. Usual care for high-risk patients with diabetes and onychomycosis is completely symptomatic with frequent shaving and clipping of the nails. No effective curative local therapies exist, and systemic agents are often withheld due to concerns for side effects and interactions.

**Methods/Design:**

The primary aim is to evaluate the efficacy of four sessions of Nd:YAG 1064 nM laser application on the one-year clinical and microbiological cure rate in a randomized, double-blind, sham-controlled design with blinded outcome assessment. Mandatory inclusion criteria are diagnosis of diabetes, risk factors for developing foot ulcers defined as a modified Simm’s classification score 1 or 2 and either neuropathy or PAD. A total of 64 patients are randomized to intervention or sham treatment performed by a podiatrist.

**Discussion:**

This study will be the first double-blind study that investigates the effects of local laser therapy on onychomycosis, specifically performed in patients with diabetes with additional risk factors for foot complications.

**Trial registration:**

Clinical trials.gov as NCT01996995, first received 22 November 2013.

## Background

The prevalence of onychomycosis is 2.5 to 2.8 times higher in patients with diabetes [1-3]. The combination of onychomycosis with other risk factors, like neuropathy, increases the risk of developing diabetes-related foot complications [4]. Onychomycosis leads to thickening and sharpening of the nails. Thickening of the nails potentially increases subungual pressure and compromises vascular flow [5,6]. Sharpening of the nails can lead to small skin injuries, which are potential portals of entry for pathogens. In the presence of neuropathy and/or peripheral arterial disease (PAD), onychomycosis is an additive risk factor for diabetes-related foot complications like foot ulcers, cellulitis, osteomyelitis and gangrene [7-10]. Worldwide, foot ulcers in patients with diabetes are the leading cause of hospitalizations and amputations [11-15]. The development of foot ulcers has been associated with considerable disability [16-18], and the presence of onychomycosis has been associated with various emotional and social problems [19-23].

Treating onychomycosis is increasingly recognized as a potential strategy for preventing diabetes-related foot complications [5,24-26]. As part of the national Dutch foot care program, usual care for patients with onychomycosis is symptomatic; every six weeks, nails are skived to normal proportions and sharp edges are clipped and removed. This podiatric treatment aims to prevent ulcer formation and the development of infections through reducing subungual pressure and sharpen nails. Although effective systemic antifungal agents are available, they are often withheld due to concerns of side effects and interactions [27]. Furthermore, studies that investigated antifungal agents mostly excluded patients with diabetes. Despite many claims of efficacy, no proven effective local therapies exist. An effective and safe curative treatment option for onychomycosis could lead to a decrease in diabetes-related foot complications, especially in patients with other risk factors. By reducing the frequency of ‘skiving and clipping’ treatment sessions and by reducing the development of ulcers and infections caused by treatment-resistant onychomycosis, local therapies could become valuable preventive treatment option [28].

Local laser therapy is becoming increasingly popular as a treatment modality for a variety of dermatologic conditions and is being applied in the treatment of onychomycosis [29]. The use of lasers for improving toenail appearance has become one of the most rapidly approved therapies by the US Food and Drug Administration (FDA) [29]. Unlike pharmacologic agents, laser systems are presumed to have predictable adverse effects [29]. There are few nonrandomized trials and very few randomized studies investigating effect of laser therapy on onychomycosis. None had a double-blind design, and none were performed in patients with diabetes who also had additional risk factors for foot ulcers [29].

The primary aim of this trial is to evaluate the efficacy of four sessions of N-YAG 1064nM laser application on the one-year complete cure rate of onychomycosis in patients with diabetes and risk factors for developing diabetes related foot complications. Secondary outcomes are microbiologic cure rate and improvement in health-related quality of life (HRQOL).

## Methods/Design

Primary and secondary care patients with type 1 and type 2 diabetes mellitus with risk factors for developing diabetic foot ulcers and a clinical suspicion of onychomycosis will be recruited from a single-center podiatry practice. Patients will be included after written informed consent and microbiologic confirmation of onychomycosis.

Nail dust is collected from the target nail for microbiologic confirmation with blankophor microscopy, culture and polymerase chain reaction (PCR). PCR is regarded as the gold standard. The PCR is a real-time multiplex PCR based on amplification of ribosomal internal transcribed spacer regions and identification by probes specific for *Trichophyton mentagrophytes* species complex, *Trichophyton tonsurans*, *Trichophyton violaceum*, *Trichophyton rubrum* species complex, *Microsporum canis*, *Microsporum audouinii* and *Epidermophyton floccosum* as described by Arabatzis *et al.* [30].

The target nail is the nail with the highest onychomycosis severity index. The severity of onychomycosis is evaluated with the onychomycosis severity index (OSI) and standardized photographs are made [31]. Evaluation of treatment results will be done by an independent expert panel blinded for treatment allocation. The three experts are experienced health care providers who have experience in the treatment of patients with diabetic foot problems. Health-related quality of life (HRQOl) is evaluated at baseline and after follow-up with a generic questionnaire, the WHO-5, and a disease specific questionnaire the NailQOl [23]. The trial has received research ethics board approval from METC Isala Zwolle (NL46084.075.13/METC nr 13.0885).

### Study endpoints

The primary endpoint is complete cure rate of the target nail. Complete cure is defined as a completely normal nail, or negative microbiological results in case minor abnormalities are present. A minor abnormality is defined as an irregularity of the nails with less than 5% of the surface area of the target nail at less than 1/4 of the distance of the distal nail edge without hyperkeratosis. Secondary endpoints are microbiologic cure rate of the target nail, complete clinical cure of all affected toes, complete clinical cure of the target nail, markedly clinically improvement of the target nail, onychomycosis severity index below 6 (in patients with scores >6 at study entry) of the target nail, changes in the affected surface of the target nail, changes in affected surface of all nails with a clinical diagnose of infection, free of subungual hyperkeratosis and changes in HRQOL. A ‘markedly clinical nail improvement’ is defined as a nail with less than 10% abnormalities and without hyperkeratosis after 52 weeks.

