### Clinical follow-up

Patients are treated with laser session in week 0, 2, 4, and 12. The settings are*;* 1064 nm, spot size 3 mm, 20 J /cm2, 5 Hz, power 10 W. A maximum of two sequential sessions (one session on the horizontal and one the vertical passing) will be applied to eliminate potential safety issues in those patients with a lack protective sensibility.

After 52 weeks, complete regrowth of the nail can be expected. At baseline, 30 and 52 weeks all target nails are sampled for blankophor microscopy, culture and polymerase chain reaction.

At baseline, 30 and 52 weeks, all nails are evaluated using the following scale: completely healed, markedly improved (less than 10% affected), minor improvement, unchanged, and worse, and with the onychomycosis severity index [31]. The microbiological outcomes from week 30 are used to differentiate re-infection from persistent infection. Patients with re-infection have negative microbiological results at week 30 and positive results at week 52. Patients in whom different organisms at baseline and week 30 or 52 are isolated are regarded as having a reinfection. Patients are regarded as having a persistent infection when baseline, week 30 and week 52 microbiological results provide evidence of the same organism. Week 52 results, including the microbiological results, are used for evaluation of the primary and secondary outcomes. See Table 2 for the follow-up survey.

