### Data analysis

Estimating the proportion of patients with a complete cure rate to be 40% in the intervention group and 5% in the control group [27], with a power of 0.85, an alpha of 0.05 (2-tailed), the sample size should be at least 56. Accounting for loss to follow-up, the total sample size will be aimed at 64.

Data entry is done in duplicate by persons not otherwise involved in the study. All statistical analyses are carried out by a statistician blinded for treatment allocation. The Fisher’s Exact test will be used to test for differences between the treatment groups, and 95% confidence intervals (CIs) will be constructed for the differences in clinical and microbial cure rates. Normally distributed continuous variables will be compared using the Student *t*-test, and non-normally distributed variables will be compared with the Mann-Whitney *U* test. A significance level of less than 5% is regarded as significant. Analyses will be performed according to the intention-to-treat principle. Separate per-protocol analyses are planned in patients in whom all treatment sessions are performed and for analyses excluding re-infection. A sensitivity analysis is planned that regards completely cured patients at week 30 who have a new infection at week 52 as having a complete cure. All endpoints are evaluated at week 52.

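### The only listed OSI endpoint is a below-6 cut in a baseline subset, which costs power in a secondary comparison that data already collected could recover

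*Protocol article*

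**What the plan says.** Under Clinical follow-up the protocol states: "At baseline, 30 and 52 weeks, all nails are evaluated using the following scale". It then names a five-level rating and the OSI: "completely healed, markedly improved (less than 10% affected), minor improvement, unchanged, and worse, and with the onychomycosis severity index". Methods/Design also uses the OSI to choose the nail on which outcomes are judged: "The target nail is the nail with the highest onychomycosis severity index". The OSI is therefore a rankable score, available for every target nail at entry and at week 52.

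Study endpoints lists one OSI endpoint: "onychomycosis severity index below 6 (in patients with scores >6 at study entry) of the target nail". Neither week-52 OSI nor change in OSI is listed. The same list does treat other measures as changes, for example "changes in the affected surface of the target nail" and health-related quality of life.

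Under Data analysis, "The Fisher’s Exact test will be used to test for differences between the treatment groups". The t-test and the Mann-Whitney U test are provided for continuous variables.

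**The concern.** Under this endpoint, a target nail that falls from a high score to 7 counts the same as one that stays put or worsens. A patient who enters at 6 or lower contributes nothing, although the score is recorded. The protocol gives no reason for handling the OSI this way while analysing affected surface as a change.

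The analysable sample is small, about 56 patients. The Discussion says that a finding of non-efficacy would be at least as relevant as a positive one. A non-significant Fisher test in part of that sample cannot separate no effect on severity from partial improvement. A mean difference in OSI with a confidence interval, in all patients, would put a limit on the effect.

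**Working it through.** **1. The plan's own figure.** Inputs from Data analysis: 40% versus 5% complete cure, power 0.85, two-sided alpha 0.05, total of at least 56. Exact power of Fisher's test by full enumeration, assuming equal arms:

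- 27 per arm: 0.840
- 28 per arm: 0.860

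So 56 is the smallest equal-arm total that reaches 0.85, and the stated figure reproduces. The target of 64 implies 12.5% loss (56/0.875 = 64). No power is stated for the OSI endpoint. The checks below use 28 per arm.

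**2. Efficiency kept by the cut.** Let q be the share of controls below 6 at week 52, and f the share of patients above 6 at entry. The protocol gives neither, so both are assumptions. For a normally distributed score and a small shift, the cut keeps φ(z_q)² / [q(1 − q)] of the efficiency of a comparison of means:

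| q | φ(z_q) | Calculation | Kept |
|---|---|---|---|
| 0.50 | 0.399 | 0.1592/0.25 | 0.64 |
| 0.30 | 0.348 | 0.1209/0.21 | 0.58 |
| 0.20 | 0.280 | 0.0784/0.16 | 0.49 |
| 0.10 | 0.175 | 0.0308/0.09 | 0.34 |
| 0.05 | 0.103 | 0.0106/0.0475 | 0.22 |

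The best case is 0.64, a loss of 36%. The subset restriction multiplies this by f, approximately:

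- q = 0.5, f = 0.8: 0.64 × 0.8 = 0.51
- q = 0.3, f = 0.8: 0.58 × 0.8 = 0.46
- q = 0.1, f = 0.6: 0.34 × 0.6 = 0.21

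Over q from 0.1 to 0.5 and f from 0.6 to 1, the share kept runs from about 0.21 to 0.64.

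**3. Power under a graded response.** Each assumed pair of below-6 rates corresponds to a normal shift of z(laser rate) − z(control rate). The full-score column is a two-sample t-test on that shift. The last column assumes that 25% of patients enter at 6 or lower, leaving 28 × 0.75 = 21 per arm.

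| Below 6, laser vs sham | Shift (SD) | Full score, 28 per arm | Fisher, 28 per arm | Fisher, 21 per arm |
|---|---|---|---|---|
| 40% vs 5% | 1.39 | 0.999 | 0.860 | 0.745 |
| 25% vs 5% | 0.97 | 0.946 | 0.387 | 0.324 |
| 40% vs 15% | 0.78 | 0.821 | 0.454 | 0.327 |
| 60% vs 30% | 0.78 | 0.815 | 0.508 | 0.360 |

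**4. Power under an all-or-none response.** This is the least favourable case for the full score. A simulation used 28 per arm and 800 replicates per setting. It assumed a baseline SD of 6 and 5% or 25% of patients entering at 6 or lower. Cured nails went to 0, and the others stayed at baseline plus noise of SD 3. Fisher's test on the cut in the subset was compared with a baseline-adjusted linear model in all patients, with robust standard errors:

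| Cured, laser vs sham | Cut, subset | Adjusted OSI, all patients |
|---|---|---|
| 40% vs 5% | 0.64–0.81 | 0.73–0.82 |
| 25% vs 5% | 0.26–0.36 | 0.36–0.45 |
| 40% vs 15% | 0.30–0.43 | 0.38–0.48 |

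The gain is about 1 to 10 percentage points. The simulated score was bounded by assumption. Repeating the simulation without an upper limit gave the same picture.

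**The case against.** The strongest reply is that little turns on this. The OSI endpoint is one of nine listed secondary endpoints and carries no power claim. The stated aim is complete cure, so a conclusion of non-efficacy would rest mainly on the primary endpoint. Graded benefit is not lost to the trial: changes in affected surface of the target nail and of all infected nails are listed, freedom from subungual hyperkeratosis is a separate endpoint, and quality of life is analysed as change. This stands. A reader might infer that the trial would miss partial improvement altogether, and the listed endpoints do not support that.

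A reader might also infer that the cut throws away most of the information in the score. That depends on figures the protocol does not give. With a central cut and nearly all patients above 6 at entry, up to 0.64 of the efficiency is kept. The larger power gaps assume a graded shift across all patients, whereas the design assumption is a difference in cure rates.

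Restricting to patients above 6 at entry is coherent, because someone already below the threshold cannot newly reach it. It selects on a baseline value, so it does not bias the randomised comparison; its cost is precision only.

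Finally, an analysis plan that is not shown could add an analysis of the whole score. So it is established only that the listed OSI endpoint is a cut, not that no other OSI analysis is intended. The endpoint as listed is still a stated choice, and it can be improved where it stands.

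**Conclusion.** The point holds as a limited, inexpensive improvement to a secondary endpoint. Under a normal score with a graded shift, the listed endpoint loses at least 36% of the efficiency. It loses more than half if about 20% or fewer of controls fall below 6. Even at the most favourable cut, it also loses more than half if over about a fifth of patients enter at 6 or lower (0.5/0.64 = 0.78). Under an all-or-none response, the loss is about 1 to 10 points of power. Which case applies cannot be settled from the protocol, because it gives no OSI distribution, no share entering above 6 and no expected shift. The primary endpoint, the sample size of 56 (64 with loss) and the validity of the randomised comparison are not in question.

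**What to change.** In Study endpoints, define the OSI secondary endpoint as the week-52 OSI of the target nail in all randomised patients. Analyse it by a linear model on treatment and baseline OSI, and report the adjusted difference with its 95% confidence interval. If the score is clearly non-normal, use the Mann-Whitney U test on change from baseline, which is already among the planned methods. Keep OSI below 6 among those above 6 at entry as a supportive responder summary. Leave the primary endpoint as it is.

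An ordinal analysis of the five-level week-52 rating of the target nail could be added on the same reasoning. It is optional and would lengthen the secondary list by one comparison.

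The cost is a change of wording, since the scores are already collected at baseline and week 52. The one drawback is that a mean score difference is harder to read than a responder rate, which is why the responder rate should stay beside it.

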### Patient selection criteria

Patients with clinical suspicion and microbiologic confirmation of onychomycosis are randomized to laser treatment or sham, see Figure 1.

**Figure 1 Fig1:**
[figure not shown]
**Study flow chart.**

Mandatory inclusion criteria are diagnosis of T1DM or T2DM, 18 years or older, at risk for diabetic foot ulcers defined by a modified Simm’s classification score 1 or 2 with either neuropathy or PAD [32], and nail involvement of at least 25% of the target nail [3]. See Table 1 for the modified Simm’s classification.

**Table 1 Tab1:** **The modified Simms’ classification**

**Simm’s classification**	**Risk profile**	**Control frequency**
Simm’s 0	No loss of PS or PAV	Once in 12 months
Simm’s 1	Loss of PS or PAD, Without signs of local increased pressure	Once in 6 months
Simm’s 2	Loss of PS and PAD. Loss of PS and/or PAD in combination with signs of local increased pressure.	Once in 3 months
Simm’s 3	Ulcer or amputation in the medical history	Once in 1 to 3 months

PAD, peripheral arterial disease; PS, protective sensibility.

Exclusion criteria are no microbiologic confirmation, Simms’ classification score 3, the presence or history of diabetic foot ulcers, ischemic pain, ankle brachial index <0.9, patients receiving dialysis, severe renal insufficiently (eGFR below 30 ml/min), a documented toe pressure below 50 mmHg, use of systemic or topical antifungal agents 3 months prior to inclusion, use of immunosuppressive drugs, presence of psoriasis, lichen planus, or other abnormalities that could result in clinically abnormal toenails, a history of epilepsy and insufficient knowledge of the Dutch language. Patients with a dark skin color (Fitzpatrick 4 and 5) are excluded since dark skin color is associated with dark nails, which theoretically lead to increased temperatures during laser application [33].

### Treatment assignment

Patients will be randomized in blocks using sealed nontransparent envelopes to either laser or sham treatment. A cloth between the head and his or her feet and a blinded goggle (which also protects the eyes) is used for blinding the subjects. The periprocedural sounds and lights during the laser application and the sham procedure are identical. The investigators are blinded for treatment allocation through the use of an independent second podiatrist who performs the interventions. An independent three-person panel blinded for treatment allocation evaluates the study outcomes using standardized photographs made at baseline, week 30 and at the end of follow-up. When consensus cannot be reached, decisions are made through majority voting.

### Clinical follow-up

Patients are treated with laser session in week 0, 2, 4, and 12. The settings are*;* 1064 nm, spot size 3 mm, 20 J /cm2, 5 Hz, power 10 W. A maximum of two sequential sessions (one session on the horizontal and one the vertical passing) will be applied to eliminate potential safety issues in those patients with a lack protective sensibility.

After 52 weeks, complete regrowth of the nail can be expected. At baseline, 30 and 52 weeks all target nails are sampled for blankophor microscopy, culture and polymerase chain reaction.

At baseline, 30 and 52 weeks, all nails are evaluated using the following scale: completely healed, markedly improved (less than 10% affected), minor improvement, unchanged, and worse, and with the onychomycosis severity index [31]. The microbiological outcomes from week 30 are used to differentiate re-infection from persistent infection. Patients with re-infection have negative microbiological results at week 30 and positive results at week 52. Patients in whom different organisms at baseline and week 30 or 52 are isolated are regarded as having a reinfection. Patients are regarded as having a persistent infection when baseline, week 30 and week 52 microbiological results provide evidence of the same organism. Week 52 results, including the microbiological results, are used for evaluation of the primary and secondary outcomes. See Table 2 for the follow-up survey.

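### The different-organism rule for re-infection omits the condition that week 52 is positive, so the analysis excluding re-infection can drop patients who are negative at week 52

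*Protocol article*

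**What the plan says.** The article's Clinical follow-up section sets three microbiological rules.

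- Re-infection, first rule: "Patients with re-infection have negative microbiological results at week 30 and positive results at week 52".
- Re-infection, second rule: "Patients in whom different organisms at baseline and week 30 or 52 are isolated are regarded as having a reinfection".
- Persistent infection: "Patients are regarded as having a persistent infection when baseline, week 30 and week 52 microbiological results provide evidence of the same organism".

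The label is used under Data analysis: "Separate per-protocol analyses are planned in patients in whom all treatment sessions are performed and for analyses excluding re-infection". The visit that decides the endpoints is week 52: "Week 52 results, including the microbiological results, are used for evaluation of the primary and secondary outcomes". Under Study endpoints, "Complete cure is defined as a completely normal nail, or negative microbiological results in case minor abnormalities are present".

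**The concern.** The first rule makes re-infection a week-52 state: the patient must be positive then. The second rule drops that requirement, because a different organism at week 30 is enough by itself. The label can therefore attach to someone who is free of infection at the visit that counts.

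An analysis that excludes re-infection makes sense as a way of setting aside week-52 failures due to a new infection. If it also sets aside week-52 successes, it no longer answers that question, and its cure rate is pulled down. If it sets aside failures in whom the baseline organism is present at week 52, its cure rate is pulled up.

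**Working it through.** **Inputs.** The three rules above; week 52 as the deciding visit; and the sampling plan, "At baseline, 30 and 52 weeks all target nails are sampled for blankophor microscopy, culture and polymerase chain reaction". The PCR is a multiplex with several species targets (Methods/Design), so one sample can show more than one organism.

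**Enumeration.** Take organism A at baseline and one possible second organism B. Weeks 30 and 52 can each be negative, A, B or A+B, giving 4 × 4 = 16 patterns. The phrase about different organisms can be read in two ways:

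- strict: at week 30 or 52, organisms are found and none is shared with baseline;
- broad: any organism not seen at baseline is found at week 30 or 52.

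In the table, R is re-infection, P is persistent infection and a dash is neither.

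| Week 30 (rows), week 52 (columns) | negative | A | B | A+B |
|---|---|---|---|---|
| negative | – | R (first rule only) | R | R |
| A | – | P | R | P; broad: also R |
| B | **R** | R | R | R |
| A+B | –; broad: R | P; broad: also R | R | P; broad: also R |

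Counts by reading:

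| | Strict | Broad |
|---|---|---|
| Labelled re-infection, either rule | 3 + 1 + 4 + 1 = 9 | 3 + 2 + 4 + 4 = 13 |
| of these, negative at week 52 | 1 | 2 |
| of these, also persistent | 0 | 3 |

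A / B / negative is labelled re-infection on both readings. It is a microbiologic cure at week 52, and a complete cure as well if the nail is normal or has only minor abnormalities. A / B / A is also labelled re-infection on both readings, with the baseline organism present at week 52. If both A and B are present at baseline, the second rule is not triggered by either of them.

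These are counts of possible patterns. They say nothing about how many patients will show each one.

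**Effect of one patient.** The plan's minimum of 56 patients reproduces: with 40% against 5%, two-sided alpha 0.05 and Fisher's exact test, power is 0.840 at 27 per arm and 0.860 at 28 per arm. Assuming equal arms of 28, the expected laser cures are 0.40 × 28 = 11.2, taken as 11, and the sham cures 0.05 × 28 = 1.4, taken as 1.

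- Nobody dropped: 11/28 = 39.3%.
- One complete cure dropped: 10/27 = 37.0%, about 2.2 points lower.
- One failure dropped: 11/27 = 40.7%, about 1.5 points higher.
- Two failures dropped: 11/26 = 42.3%, 3.0 points higher.

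Against 1/28 on sham, Fisher's p is about 0.002 for 11/28 and for 10/27, and below 0.001 for 11/27 and 11/26.

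**The case against.** The best defence is context. The paragraph says that week-30 microbiology serves to tell re-infection from persistent infection, a question that arises only in patients still infected. The rule just before requires a positive week 52, and the sensitivity analysis under Data analysis speaks of new infection at that visit. Read together, a patient negative at week 52 would fall in neither category. That is plausible and may be what the authors meant. It does not remove the explicit week-30 alternative from the second rule, and whoever codes the label must either follow the sentence or depart from it.

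Other parts of the defence stand.

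- A reader might infer that the two categories overlap as a matter of fact. The article does not support that: the overlap needs mixed results and the broad reading, and on the strict reading it vanishes. Precedence for mixed results may also be settled in a full protocol or SAP that is not shown.
- A / B / A is less clear-cut than A / B / negative, because the first rule already treats return of the same organism after a negative week 30 as re-infection.
- A reader might also infer that one to three patients per arm are affected, by assuming that 3% to 10% of patients have a second organism (0.03 × 28 = 0.84 to 0.10 × 28 = 2.8). The article gives no such frequency. The assumption counts anyone with a second organism, and the mislabelled patterns are only part of that group. To lower the complete cure rate, the patient must also be negative at week 52 with a normal or near-normal nail.
- The shifts are small beside the planned 35-point difference, and none of the illustrative comparisons loses significance.

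**Conclusion.** The point holds in a limited form. As written, the second re-infection rule labels A / B / negative as re-infected and so removes a week-52 microbiologic cure from the analysis excluding re-infection. This is true on both readings of different organisms, and only a contextual reading that sets aside the stated week-30 alternative avoids it. The rule also labels A / B / A as re-infected. Double classification as re-infected and persistent is conditional on the broad reading.

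The number of patients affected cannot be computed from the article and is probably low. Each one moves the laser cure rate by roughly 1.5 to 2 points, assuming 28 per arm and 11 cures. The consequence is confined to the analyses excluding re-infection and possibly the sensitivity analysis on new infection. The intention-to-treat primary comparison and the week-52 secondary endpoints do not use the label, so nothing here supports a claim that the main result is at risk.

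**What to change.** In Clinical follow-up, replace the second re-infection rule and the persistence rule with wording such as:

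*Patients with a positive week-52 result in whom the baseline organism is not found at week 52 and a different organism is found are regarded as having a re-infection. Patients negative at week 52 are never classed as re-infected and stay in the analysis excluding re-infection. Patients positive at week 30 (any organism) in whom the baseline organism is found at week 52, alone or with another organism, are classed as persistent.*

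Keep the rule for a negative week 30 followed by a positive week 52 unchanged. Compare organisms by PCR where the organism is a PCR target, and by culture at both visits for organisms outside the panel.

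Applied to the 16 patterns, this gives 4 negative at week 52 (neither label), 6 re-infections (negative then A, B or A+B; and A, B or A+B then B) and 6 persistent (A, B or A+B at week 30, then A or A+B). The total is 4 + 6 + 6 = 16, with no overlap and no gap. Placing A / B / A and A / B / A+B under persistent infection is a convention, but it is fixed in advance.

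The cost is one short paragraph, agreed before labels are assigned. All samples are already planned. The downside is that slightly fewer patients are classed as re-infected.
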